##### **3.2.2 Secondary efficacy outcome measures**

- 3.2.2.1 The secondary aim of identifying genes correlated with nutritional supplementation with lycopene or fish oil will be accomplished by analyzing gene expression of 30,000 human genes using a cDNA array. Identification of a gene cluster associated with lycopene or fish oil but not placebo will be

accomplished using hierarchical clustering[62], or alternate algorithms that use permutation t-test statistics to account for the multiplicity of tests accomplished using such large scale microarrays[63]. If sufficient nucleic acid samples remain after primary outcome measure assessment, and microarray analysis, confirmatory Taqman quantitative polymerase chain reactions will be used to confirm the specific induction of genes identified in these studies by lycopene or fish oil.

- 3.2.2.2 To accomplish the secondary aim of identifying genes correlated with baseline dietary intake, patients will be stratified for high and low intake of total energy, fat/meat/animal products, dairy/calcium, fish, vegetables, tomatoes/lycopene, vitamin E, and selenium as defined by the Willett Semi-quantitative Food Questionnaire. Separate microarray data analyses will be performed for each dietary factor by placing all patients with low intake ( $\leq$  median) into the first half of the data table, and subsequently all patients with high intake ( $>$  median). The same standard microarray hierarchical clustering and permutation t-test approaches as in 3.2.2.1 will then be used to identify genes whose expression differs between these groups.
- 3.2.2.3 We acknowledge that the study is underpowered to assess effects of nutrition supplementation on progression rates, given the heterogeneous nature of prostate adenocarcinoma. Nevertheless, it is compelling to perform exploratory data analysis to examine whether exploratory analysis may detect genes correlated with progression or lack of progression at 12 months in the MENS study. If any correlates are detected, they will be used to formulate a hypothesis for testing in further large scale studies, such as the multi-institutional CALBG or SWOG watchful waiting trials.
- 3.2.2.4 With watchful waiting, approximately 25% of patients will experience disease progression when assessed 12 months after study entry. To assess whether the

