94C for 4 minutes to denature the DNA, and applied to the slide under a 25x40 mm cover slip (lifter slips, Eerie Scientific). Hybridization reactions will be allowed to proceed at 63.5C for 14-16 hours with slides contained in a Plexiglas chamber (HybeChamber, Genemachines, Redwood City, CA) submerged in a water bath. After hybridization, each slide will be washed in 2X SSC, 0.2% SDS for 5 minutes at 65C in a Coplin jar, followed by 4 minutes in 2X SSC at room temperature on a gently agitating rotator platform, and 1 minute in 0.065X SSC at room temperature. Excess liquid will be removed from slides by spinning at 600 rpm in a Beckman Allegra clinical centrifuge.

Arrays will be imaged with a confocal laser scanning microscope (Axon 4000B). Post image-acquisition data analysis will be performed with Genepix 3.0 software (Axon), and ratio information corrected for background fluorescence will be uploaded into a relational database (NOMAD, Derisi lab, UCSF unpublished) housed on the laboratory Linux web server. NOMAD will then be queried to produce normalized datasets that can be manipulated by other analysis algorithms. There is no consensus on how to normalize array data across groups working in gene expression profiling. Our approach, implemented by NOMAD software is to make the sum of signals in each channel, cy3 and cy5, equal. Though it may be that more up- or down-regulation is present in the cy3 or cy5 channels for a particular nutritional intervention, we assume that averaging across the large number of genes present on each array will allow identification of modulated genes. The identification of *caspase-3* regulation in prostate cancer attests to the practicality of this approach (unpublished data, [name] lab).

Initial microarray studies will collate sets of named and novel genes that are differentially expressed according to baseline dietary intake quartiles using supervised and unsupervised hierarchical cluster analysis[62] and statistical analysis for microarrays (SAM)[63], a software package that implements a permutation T-test to identify genes up- or down-regulated with a measure of statistical confidence.

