For the secondary specific aims (aims 1.2 through 1.4 defined above), we will consider a microarray dataset with measurements for 30,000 genes. For this exploratory investigation genes will be treated as being independent so as to first identify all possible genes that may indicate an effect due to the nutritional supplement (Aim 1.2) or to other dietary components (each considered as a binomial variable) (Aim 1.3). Fisher's exact test will be used to determine which genes result in differences in proportions with up or down regulated genes between groups. No adjustment for multiple comparisons will be made. Also, after all patients have had the potential to be followed for at least one year, they will be classified as to whether they had experienced disease progression within 1 year from protocol entry. The same exploratory techniques described above first using the baseline gene expression profile will be carried out to identify genes that may be associated with disease progression (Aim 1.4). Even though any nutritional supplement will be stopped at 3 months from the start of protocol therapy and the duration of any effect is unknown, this analysis will be repeated using the 3-month gene expression profile to identify the effects of any gene that might have been modified by protocol treatment. To account for genes with highly variable expression regardless of study arm, genes whose expression levels change two-fold in more than 20% of men on placebo (comparing three-month to baseline) will

be excluded from subsequent consideration. This might exclude possible predictors of outcome, but if there is variability within the placebo group then the results may be biased. This refining process will isolate potential predictors of nutritional change when assessing the primary as well as the secondary outcomes. Standard microarray gene expression software algorithms will facilitate analyses to determine if there are individual genes or clusters of genes associated with either supplement, dietary component or disease progression[62, 63] . Fisher's exact test will be used to determine which genes result in statistically significant differences between the groups.

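### For the 30,000-gene array aims the protocol both accounts for multiplicity and rules out adjustment, and does not say which analysis decides the gene lists

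*Protocol*

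**What the plan says.** **Section 3.2.2.1 (Aim 1.2)** offers hierarchical clustering or, as an alternative, algorithms that use "permutation t-test statistics to account for the multiplicity of tests accomplished using such large scale microarrays". **Section 3.2.2.2 (Aim 1.3)** carries the same approaches over to diet and forms two groups at the median, "placing all patients with low intake" first and high intake after.

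**Section 8.2, Baseline assessment—Molecular,** names SAM, a permutation method. There the diet analysis looks for genes "differentially expressed according to baseline dietary intake quartiles".

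**Section 13 (Aims 1.2 to 1.4)** starts from "we will consider a microarray dataset with measurements for 30,000 genes". It states that "Fisher's exact test will be used to determine which genes result in differences in proportions with up or down regulated genes between groups", and then "No adjustment for multiple comparisons will be made". Each dietary component is a binomial variable. Genes that change two-fold in more than 20% of placebo men are dropped. The section then cites the clustering and SAM references again, and closes by saying that Fisher's "exact test will be used to determine which genes result in statistically significant differences between the groups".

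No per-gene significance level is given for the arrays. The only threshold in section 13 for up or down is a two-fold change from baseline to three months.

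**The concern.** The protocol settles one question twice, in opposite directions. Two analysts could each follow it faithfully and report very different lists: one from SAM with an error-rate measure attached, one from unadjusted Fisher tests at whatever level the analyst picks. Because the closing sentence of section 13 gives the decision to Fisher, the second list is the one that would be called statistically significant.

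The lists have a use. Section 3.2.2.1 sends genes to confirmatory PCR only if nucleic acid remains, and section 8.2 puts the yield at 100-600 ng of RNA from a core biopsy. Section 3.2.2.3 wants progression correlates to seed hypotheses for large multi-institution trials. A list of unknown false-positive content is a poor guide to spending that material.

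Two smaller gaps sit beside this one. Quartiles and a median split are different analyses. And for Aim 1.3 and the baseline part of Aim 1.4, no cut-off is stated for calling a gene up or down.

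**Working it through.** The protocol gives no expected number of false genes, so there is no figure of that kind to reproduce. The design figures used as inputs do reproduce: 87 / 0.9 = 96.7, so 97 accrued; and 29 per arm with a one-sided Fisher test at .025 for 60% against 20% has exact power 83.0%, slightly above the stated 81%.

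**Contrasts.** 2 supplement (each arm against placebo) + 8 diet factors (section 3.2.2.2) + 2 progression (baseline profile, then three-month profile, section 13) = 12.

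**Group sizes from 87 evaluable men.** Supplement: 29 v 29. Diet at the median: 43 v 44. Progression at the 25% given in section 13: 0.25 × 87 ≈ 22, so 22 v 65.

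**Assumptions.** All genes null; two-sided .05, with .025 as the alternative; a common up-or-down rate p, which the protocol does not give, varied from 2% to 50%.

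**Formula.** Expected false genes per contrast = 30,000 × actual size of Fisher's test, found by enumerating all 2×2 tables. This expectation does not need genes to be independent. The simple product 30,000 × 0.05 = 1,500 per contrast (18,000 over 12) is only a ceiling, because Fisher's test is conservative here.

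**Placebo filter.** A gene is kept if at most 5 of 29 placebo men change (5/29 = 17%; 6/29 = 21%). For the supplement contrasts, rejection and survival of the filter are enumerated jointly. For the other ten, the count is multiplied by the share kept, which assumes that filter status is unrelated to those contrasts and that the same p applies at baseline.

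Total = 2 × supplement (filtered) + share kept × (8 × diet + 2 × progression).

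At two-sided .05:

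| p | share kept | supplement, unfiltered | supplement, filtered | diet, each | progression, each | 12-contrast total, unfiltered | 12-contrast total, filtered |
|---|---|---|---|---|---|---|---|
| 2% | 1.000 | 1 | 0 | 23 | 180 | 550 | 549 |
| 5% | 0.997 | 39 | 19 | 327 | 638 | 3,967 | 3,918 |
| 10% | 0.936 | 260 | 130 | 888 | 771 | 9,168 | 8,357 |
| 15% | 0.738 | 486 | 243 | 1,029 | 861 | 10,929 | 7,834 |
| 20% | 0.463 | 636 | 317 | 1,016 | 941 | 11,278 | 5,271 |
| 30% | 0.093 | 752 | 319 | 1,109 | 1,049 | 12,477 | 1,660 |
| 40% | 0.008 | 721 | 99 | 1,114 | 1,244 | 12,841 | 289 |
| 50% | 0.0003 | 746 | 6 | 974 | 1,208 | 11,697 | 16 |

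(Diet and progression columns are before the filter.) Example at 10%: 2 × 130 + 0.936 × (8 × 888 + 2 × 771) ≈ 8,360, which is 8,357 before rounding.

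At two-sided .025 the filtered totals are 1,242 (5%), 3,200 (10%), 3,447 (15%), 2,551 (20%) and 846 (30%). At 2% the total is 193.

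The filter lowers the count but does not control error. At p = 30% it keeps 9.3% of genes, and 11.4% of those kept are falsely called in a supplement contrast, because the filter selects genes with few placebo changes by chance.

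**The case against.** **The work is exploratory and openly unadjusted.** Section 13 says so, PCR confirmation is foreseen, and progression correlates serve only to form hypotheses. This stands as a limit on consequence. It does not tell the reader which method decides, nor does it justify calling an unadjusted result statistically significant.

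**Section 13 does not discard the permutation methods.** Correct. A reader might infer that Fisher tests replace SAM, but section 13 cites the same clustering and SAM references, and section 3.2.2.1 offers permutation only as an alternative to clustering. A Fisher screen followed by SAM is a possible reading; the protocol just does not state it.

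**Fisher's test can be applied at baseline.** One might conclude that with no pre/post change there is nothing to classify. But section 8.2 hybridises each sample against a reference pool and stores ratios, so a gene can be called up or down relative to the pool. Only the cut-off is missing.

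**An unadjusted list can still be ranked.** True. The usual p-value adjustments keep the order. What is lost is knowledge of how many entries are false.

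**The unfiltered counts overstate the problem.** Also true. Totals of 9,000 to 13,000 ignore the placebo rule, and most of any total comes from the diet and progression contrasts.

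**Conclusion.** The contradiction is real and lies in the protocol itself, so it is not detail left to an analysis plan. With the placebo filter applied, at an assumed two-sided .05 and all genes null, expect about 20 to 320 false genes per supplement contrast at change rates of 5-30%. Over all 12 contrasts, expect about 3,900 to 8,400 at rates of 5-20%, or about 1,200 to 3,400 at .025. The total falls below 1,000 when rates are near 2%, or when they are so high that the filter removes nearly all genes (40% at .05; already 30% at .025).

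These figures rest on a level and event rates that the protocol does not state. A reader might infer thousands of false genes from each comparison. The enumeration does not support that: thousands describes the sum over 12 contrasts, not any one of them. Nor does the multiplicity conflict reach the primary IGF-1 and COX-2 comparisons, which have their own level and sample size. This is a secondary-aim defect that should be corrected before the array data are analysed.

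**What to change.** In section 13:

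- Delete "No adjustment for multiple comparisons will be made".
- Name SAM, already cited, on continuous log ratios as the deciding analysis for Aims 1.2 to 1.4. Report lists at a pre-stated false discovery rate with q-values.
- If Fisher results are kept, describe them as an unadjusted descriptive screen, state their level and the baseline cut-off against the reference pool, and do not call them statistically significant.

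In section 8.2, replace quartiles by the median split, so that it agrees with sections 3.2.2.2 and 13.

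The cost is wording only: no new patients, assays or software. The downside is shorter gene lists.

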### **8.3 Assessment during the treatment period**

#### **Follow-up assessment—Clinical**

Standardized Clinical Follow-up Protocol - At the three month follow-up, patients will undergo a standard history and physical exam including digital rectal examination performed by the treating physician. Serum and red blood cells will be drawn for PSA, testosterone, estrogen, lycopene, omega-3 fatty acid, omega-6 fatty acid, IGFBP-3, and IGF-1 levels. Patients will have a second appointment for research purposes only, with a study urologist ([name] or another urologist from the UCSF Urologic Oncology Department) who will obtain four directed prostate core needle samples under ultrasound guidance in order to re-biopsy the areas of tumor and normal prostate identified at the baseline visit to fulfill the study primary outcome measure of detecting gene expression modulation by nutrients. Tissue biopsies for research purposes will also be sent for standard pathologic examination. As obtaining biopsies three months after electing Watchful Waiting is not standard practice, the study will bear costs for the biopsy procedure. In addition to any prostate biopsy obtained above, serum and urine will be obtained and frozen for future analysis. Patients will fill out a second food diary during the second month of treatment intervention and a third food diary prior to their biopsy. These food diaries will be used to collect information about changes in dietary behavior associated with recent diagnosis with prostate cancer, dietary counseling, or participation in this trial. Patients will complete another Health and Prostate Cancer Survey after three months. Patients will also be asked to self-report their compliance with the study treatment, and to return their medicine so that pill counts can be performed. Based on the results of the three-month follow-up visit, serum and pathology tests, the treating physician will assess the patient for disease progression.

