### **9.3 Molecular**

**Primary – not applicable.**

**Secondary – not applicable.**

### **9.4 Clinical**

We define disease progression as: PSA doubling time within 3 months; any adverse pathological findings at baseline, three, six, nine, or 12 months if extended pattern biopsies are performed with a Gleason sum  $\geq 7$  (see exception below); involvement of  $> 50\%$  of any core;  $> 1/3$  of cores positive; or other incidental evidence of clinical progression (i.e. positive bone scans or lymph node biopsies). Any patient exhibiting progression at any time will be withdrawn from the study and offered standard treatment options. Any patient may also withdraw from the protocol at any time for any reason and be offered standard treatment.

If extended pattern biopsies are performed with a Gleason sum  $\geq 7$ , but with a pattern 4 seen as a microfocus ( $< 2\text{mm}$  in length), this will not exclude the patient from continuing on trial.

Regarding the 4 core research biopsies, if involvement of  $> 50\%$  of any core or  $> 1/3$  of cores are positive, this will NOT exclude the participant from continuing in the study unless a Gleason pattern 4 is seen (if Gleason pattern 4 is seen as a microfocus [ $< 2\text{mm}$  in length] this will not exclude the patient from continuing on trial).

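### Aim 1.4 relates the 3-month expression profile to progression counted from study entry, so progression found at the 3-month visit is concurrent with the profile, not predicted by it

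*Protocol*

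**What the plan says.** Section 13 defines the outcome for Aim 1.4 once all men could have been followed for a year: "they will be classified as to whether they had experienced disease progression within 1 year from protocol entry". The baseline profile is related to that class first. The protocol then states that "this analysis will be repeated using the 3-month gene expression profile", with the aim of finding genes that treatment may have modified. Its only caveat is that the supplement stops at 3 months and that the duration of any effect is unknown. When it introduces a filter for variable genes, the same paragraph speaks of prediction: "This might exclude possible predictors of outcome".

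Section 8.3 makes the 3-month visit an occasion for declaring progression: "Based on the results of the three-month follow-up visit, serum and pathology tests, the treating physician will assess the patient for disease progression". The four research cores taken at that time contribute to this: "Tissue biopsies for research purposes will also be sent for standard pathologic examination".

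Section 9.4 lists "any adverse pathological findings at baseline, three, six, nine, or 12 months" among the grounds for progression, and the text that follows ties this to extended pattern biopsies and a Gleason threshold. It adds: "Any patient exhibiting progression at any time will be withdrawn from the study and offered standard treatment options". For the four-core research biopsies it makes an exception for heavy core involvement or a high share of positive cores: "this will NOT exclude the participant from continuing in the study unless a Gleason pattern 4 is seen". A pattern 4 microfocus is also exempt.

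**The concern.** A marker measured at 3 months can be prognostic only for what happens after 3 months. Here the outcome window opens at entry, so it includes progression declared at the visit that supplies the tissue. In those men, altered expression may reflect disease already present.

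Section 3.2.2.3 intends any correlates to become hypotheses for larger watchful waiting trials. The screen covers 30,000 genes without multiplicity adjustment. Nothing in the plan separates a marker of existing progression from a marker of later progression, and a larger study with the same time origin would reproduce the confusion.

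**Working it through.** **Time order.** The protocol gives no event count or power for Aim 1.4, so there is no stated figure to reproduce. The first check sets the sections side by side.

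- Outcome window: entry to 12 months (Section 13).
- Explanatory variable: tissue taken at about 3 months (Section 13; study table in Section 8.6).
- Progression assessed at 3 months: yes, from the visit, serum and pathology (Section 8.3).
- Scheduled visits between baseline and 3 months: none (study table).
- Men who progress: withdrawn (Section 9.4).

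Three groups follow:

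1. Men found to have progressed at the 3-month visit have a profile concurrent with the event.
2. Men withdrawn before the biopsy have no profile and drop out of this analysis.
3. Men who progress later have a profile that precedes the event.

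Only the third group supports a prognostic reading. The plan pools the first with the third.

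**Size of the early group.** Inputs are 25% progression at 12 months (Section 3.2.2.4 and the interim analysis text of Section 13) and 87 evaluable men (Sections 4.4 and 13). A constant hazard is assumed.

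- Events by 12 months: 87 × 0.25 = 21.75, about 22.
- Risk by 3 months: 1 − 0.75^(3/12) = 0.0694.
- Events by 3 months: 87 × 0.0694 = 6.0.
- Early share: 0.0694 / 0.25 = 28%.

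Under this assumption 6 is a ceiling for the concurrent group, because any man withdrawn before the biopsy leaves it.

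**After a landmark at the 3-month biopsy**, under the same assumption:

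- Men at risk: 87 × (1 − 0.0694) = 81.0.
- Events remaining: 87 × (0.25 − 0.0694) = 15.7, about 16.
- Residual risk: 15.7 / 81.0 = 19.4%.

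**Effect on one gene.** A simulation took 87 men with 22 events and a two-sided Fisher exact test at 0.05, with 20,000 runs per setting. The gene has no predictive value. It is altered in 20% of all other men, but in 60% or 90% of men already progressed at the 3-month biopsy. These rates are illustrative, and every early progressor is assumed to have 3-month tissue.

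| Early events of 22 | Flagged, 60% altered | Flagged, 90% altered |
|---|---|---|
| 0 | 3% | 3% |
| 2 | 4% | 6% |
| 4 | 8% | 16% |
| 6 | 14% | 35% |
| 9 | 28% | 71% |
| 11 | 39% | 89% |

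With the landmark the rate is about 3% in every row.

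**The case against.** **The 3-month biopsy has limited power to declare progression.** Section 9.4 ties its pathology criteria to extended pattern biopsies, which Section 4.2 defines as 8 or more cores, whereas the 3-month biopsy has four. Under the exception for research cores, these end participation essentially only for Gleason pattern 4 beyond a microfocus. This stands and narrows the route. It does not close it, because Section 8.3 still has the physician judge progression on the 3-month visit, serum and pathology results.

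**The wording is mostly about association.** Aim 1.4 speaks of correlation, and the stated purpose of the repeat is to look at genes modified by treatment. This is fair, but Section 13 also refers to predictors, and the intended use is to generate hypotheses about progression.

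**Little depends on it.** Section 3.2.2.3 calls the analysis exploratory and concedes that the study is underpowered for effects on progression. With 30,000 unadjusted tests there will be many chance findings in any case. This stands as a limit on importance. Exploratory status excuses low power and multiplicity, but not a time-order error that replication would carry forward.

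A reader might infer three stronger points that the documents do not support:

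- *The early share probably exceeds 28%, because this is the only biopsy scheduled for all men after baseline.* The research-core exception and the exclusion at entry of men with a PSA doubling time under three months point the other way. The protocol gives no time distribution.
- *Many profiles are taken after the event.* Men who progress are withdrawn and no visit falls between baseline and 3 months. This could arise only in narrow cases, such as a call at the clinical visit before the separate research biopsy appointment. Missing tissue from earlier withdrawals is selection, not reversed timing.
- *The time origin causes supplement-modified genes to be confused with progression genes.* Examining modified genes is the purpose of the repeat, and a landmark would not separate the two.

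**Conclusion.** The point holds in a limited form. As written, the 3-month-profile analysis mixes men whose progression is concurrent with the profile and men who progress afterwards, so an associated gene cannot be read as prognostic.

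The 6-of-22 ceiling rests on the constant hazard and the protocol's 25%; a different time pattern could make the share smaller or larger. The simulated error rates show direction and mechanism only, since the alteration rates are assumed.

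The baseline-profile analysis does not have this flaw, and the primary endpoint is unaffected. This is a cheap improvement to an exploratory analysis, not a defect that threatens the trial.

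**What to change.** Add to Section 13: *The analysis using the 3-month expression profile is a landmark analysis. It includes only men with a 3-month biopsy and no progression at or before that visit, and counts progression after the 3-month biopsy up to 12 months from entry. Any analysis that includes events found at the 3-month visit is reported as concurrent association, not prediction.*

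No clinical rule, visit or sample changes. The cost is fewer events in an already underpowered analysis: about 16 instead of 22 under the constant-hazard assumption. The result also then applies only to men still progression-free at 3 months, which should be said when it is reported.

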### 4.4 Total number

Assuming independence of genes, 29 patients will be randomized to the lycopene intervention, 29 to the fish oil intervention and 29 to the control arm. This total evaluable sample size of 87 is sufficient to detect 60% of the intervention arm showing two-fold decrease in *IGF-1* and *Cox-2* gene expression compared with 20% of the control group. An additional 10 patients will be entered for a total planned accrual of 97, assuming a 10% dropout rate (final evaluable target number in each arm is 29). (see statistical considerations, below).

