## 13 Statistical Considerations

Patients satisfying eligibility requirements will complete a dietary questionnaire prior to randomization.

Patients will not be taking lycopene or omega-3 supplements, but other dietary sources of tomato lycopene or fish oil could possibly influence the assessment of outcome for this study. For example, it might be that an excess of tomato-consuming patients would be placed in the control arm, confounding the assessment of gene expression in response to lycopene. Therefore, patients will be stratified into four groups (low tomato/low fish, low tomato/high fish, high tomato/low fish, and high tomato/high fish) and block-randomized to placebo, lycopene, or fish oil, within these strata. This will avoid the chance occurrence of confounding due to usual intake of fish or tomato products (e.g. unbalanced patient features among the study arms). Cutoffs for the baseline dietary strata are based on the medians of intake from a **completed** independent pilot study on 96 prostate cancer patients from the source population at the UCSF Mt. Zion Cancer Center, who completed the Willett Semi-Quantitative Food Frequency Questionnaire. The median for total tomato consumption was 4 servings/week; for fish consumption it was two servings/week.

We will assess changes in serum lycopene and omega-3 fatty acid pre- and post-intervention to assess compliance and the physiologic significance of the supplementation doses.

For our primary analysis, changes in gene expression for each of the two nutrient interventions will be compared with that of the control arm. The two intervention arms will not be compared with each other. The primary outcome measure will be at least a two fold up decrease in gene expression of *IGF-1* or *COX-2* at three-months relative to the initial biopsy for a given patient (both normalized to levels of a control housekeeping gene,  *$\beta$ -glucuronidase*). To compare the intervention and control groups, we define an important difference to be a 40% difference in the proportion of patients on the intervention arm compared with the placebo arm who satisfy the primary outcome measure defined above (e.g. 20% in control vs. 60% in intervention showing at least a two-fold decrease in mRNA level). Fisher's exact test for proportions will be used to determine if *IGF-1* or *COX-2* mRNA levels are statistically significantly different between the groups.

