To evaluate the primary study aim, 29 patients will be randomized to the lycopene intervention, 29 to the fish oil intervention and 29 to the control arm. Analysis of 87 evaluable patients is sufficient to detect a 40% difference in the proportion of patients with a 2-fold decrease in *IGF-1* mRNA levels with lycopene or in the *Cox-2* gene with fish oil when compared with the control. The total accrual of 97 patients takes into consideration a 10% dropout rate by the time of the three-month biopsy. The level of significance for a directional test is set at .025 because the control group will be compared with each of the two intervention groups. The power of each test is set at 81% (nQuery).

Descriptive statistics (mean, confidence intervals, median, proportions) will be calculated to characterize the patients' baseline disease features (e.g. age, Gleason score, PSA) and self-reported nutritional dietary data within each arm. Differences between each of the intervention arms and the placebo arm will be assessed using a chi-square statistic for categorical variables, a t-statistic for continuous variables and the Mann-Whitney statistic for distributions. Estimates of the probability of remaining free of disease progression will be calculated using the Kaplan-Meier product limit method. The log rank test will be used to compare tumor progression between each supplement group and the control (Aim 1.5).

The randomized clinical trial design of this study limits the potential for confounding due to other factors, however this will be investigated by comparing the distribution of clinical parameters and other diet/lifestyle factors as well as changes after 3 months of study treatment among the three arms. Unequally distributed factors would only bias the results if they also

correlate with changes in gene expression. If necessary, the Mantel-Haenszel test for a stratified analysis would be performed in evaluating the primary study aim.

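### Section 13 extends the placebo-variability filter to the primary outcome with its cut-off at the planned placebo rate, so read literally it can remove IGF-1 and COX-2 before they are tested

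*Protocol*

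**What the plan says.** **The filter (Protocol, Section 13).** In the paragraph on the microarray aims, "genes whose expression levels change two-fold in more than 20% of men on placebo (comparing three-month to baseline) will" "be excluded from subsequent consideration". No direction of change is given, so increases count as well as decreases. Its scope is then stated: "This refining process will isolate potential predictors of nutritional change when assessing the primary as well as the secondary outcomes". Neither this section nor any other exempts the two primary genes.

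**The primary comparison (Protocol, Sections 4.4 and 13).** Each supplement arm is compared with placebo by Fisher's exact test on the proportion of men with at least a two-fold decrease, IGF-1 for lycopene and COX-2 for fish oil. Section 13 illustrates the target difference as "20% in control vs. 60% in intervention showing at least a two-fold decrease in mRNA level". Section 4.4 gives the same rates as the design basis: the sample is "sufficient to detect 60% of the intervention arm showing two-fold decrease in *IGF-1* and *Cox-2* gene expression compared with 20% of the control group".

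**The design figures (Protocol, Section 13).** "29 patients will be randomized to the lycopene intervention, 29 to the fish oil intervention and 29 to the control arm"; "The level of significance for a directional test is set at .025"; "The power of each test is set at 81% (nQuery").

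**The concern.** The filter's cut-off equals the rate of decrease that the design expects in placebo men. A gene that behaves exactly as planned therefore sits on the edge of exclusion from decreases alone, and any placebo man with a two-fold increase pushes it further over.

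An analyst who followed the text would have to check IGF-1 and COX-2 against the filter first and, if either failed, drop it. The trial could then lose one or both primary tests for a reason unrelated to whether the supplement works, and the stated power would not describe the procedure in the plan.

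**Working it through.** **Inputs**
- 29 evaluable men per arm; one-sided level 0.025 for each comparison; Fisher's exact test (Section 13).
- Two-fold decrease in 20% of placebo men and 60% of supplement men (Sections 4.4 and 13).
- Filter: more than 20% of placebo men with a two-fold change (Section 13).
- Rate u of two-fold increase in placebo men: not given. I take u = 0, the case most favourable to the plan, and then show a range.

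**1. The plan's own figures**
- The continuity-corrected two-proportion formula (0.20 vs 0.60, one-sided 0.025, power 81%) gives 28 per arm, against 29 stated.
- Exact enumeration of Fisher's test at 29 per arm gives power 0.830, about two points above the stated 81%.
- Accrual: 87 / 0.9 = 96.7, so 97, as stated.

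The design is reproduced closely, and only without the filter.

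**2. The filter in whole patients**

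5/29 = 17.2% passes; 6/29 = 20.7% is excluded. A gene is dropped at six or more placebo men.

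**3. Probability that a primary gene is excluded**

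Let X be the number of placebo men with a two-fold change, X ~ Bin(29, 0.20 + u). For u = 0:

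P(X ≤ 5) = 0.0015 + 0.0112 + 0.0393 + 0.0883 + 0.1436 + 0.1795 = 0.463, so P(X ≥ 6) = 0.537.

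| Assumed u | P(a given gene is excluded) |
|---|---|
| 0 | 0.537 |
| 5% | 0.768 |
| 10% | 0.907 |

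In the other direction, if the total change rate is only 15%, P(X ≥ 6) = 0.262; at 10% it is 0.064.

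**4. Two genes**

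With the independence that Section 4.4 assumes, and u = 0:
- at least one excluded: 1 − 0.463² = 0.785
- both excluded: 0.537² = 0.288

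**5. Power with the filter**

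Let Y be the number of supplement men with a decrease. With u = 0, sum P(X = x)·P(Y = y) over all pairs with x ≤ 5 and Fisher p ≤ 0.025, where X ~ Bin(29, 0.20) and Y ~ Bin(29, 0.60). The result is 0.455, against 0.830 when x is unrestricted. With u = 5% it is 0.229.

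**6. Dependence on the evaluable number (u = 0)**

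| Men per arm | Dropped at | P(excluded) | P(passes and rejects) | Unfiltered power |
|---|---|---|---|---|
| 27 | 6 | 0.461 | 0.517 | 0.802 |
| 28 | 6 | 0.499 | 0.487 | 0.823 |
| 29 | 6 | 0.537 | 0.455 | 0.830 |
| 30 | 7 | 0.393 | 0.585 | 0.851 |
| 31 | 7 | 0.429 | 0.556 | 0.870 |

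The step at 30 comes from the whole-number cut-off. An increase rate of 2% brings exclusion to 0.50 or above in every row.

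**7. Type I error at 29 per arm (equal true rates, u = 0)**

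| True rate | Unfiltered | Passes and rejects | Error among genes that pass |
|---|---|---|---|
| 20% | 1.06% | 1.06% | 2.3% |
| 25% | 1.20% | 1.16% | 5.0% |
| 30% | 1.25% | 1.06% | 11.4% |

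The last column is the third divided by P(X ≤ 5); at 20%, 1.06% / 0.463 = 2.3%.

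**The case against.** **The filter was meant for array genes.** Its paragraph opens with the secondary aims and a 30,000-gene dataset, and its purpose is to screen out noisy candidates. IGF-1 and COX-2 are prespecified and measured by quantitative PCR against a housekeeping gene. The descriptions of the primary analysis and its sample size mention no filter. This is a plausible account of the intent, and it stands as a reason to call the problem one of wording. It does not remove the conflict, because the sentence on scope names the primary outcome.

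**The size depends on discreteness and on assumed rates.** This stands. With decreases only, exclusion exceeds one half at 29 men but not at 27, 28, 30 or 31. Section 13 offers the 20% as an example, although Section 4.4 uses it as the design rate. The figures with u above zero rest on rates that the protocol does not supply, and a lower true placebo rate shrinks the problem.

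**A stronger reading: the filter inflates false positives in the primary test.** A reader might infer this, since genes are selected on a low placebo count and then compared with that same count. The arithmetic does not support it. A gene must both pass and reject, so the unconditional error cannot exceed that of unfiltered Fisher. Only the error rate among survivors rises. It is still 2.3% at the planned 20%, below the nominal 2.5%, and goes above nominal only when the true placebo rate is higher than about 20%. That bears on the array list, which the protocol calls exploratory and leaves unadjusted for multiplicity.

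**Conclusion.** The contradiction is real and needs correcting before analysis. As written, the plan applies to its primary genes a filter whose cut-off equals their planned placebo rate. With 29 placebo men, a 20% rate of decrease and no increases, each gene is lost with probability 0.54, and the chance of a positive primary result per gene falls from 0.83 to about 0.46. For 27 to 31 men per arm the ranges are 0.39 to 0.54 for exclusion and 0.455 to 0.585 for passing and rejecting. In none of these cases is the stated 81% delivered.

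The conclusion rests on the literal reading of scope and on the protocol's 20%. A reader might go further and say that both primary genes will probably be dropped. Under independence and no increases, the chance of losing both is 0.29; it is the loss of at least one, at 0.79, that is likely. Nor do the documents show that the authors intended the filter to govern the primary test.

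**What to change.** In Section 13, strike the reference to the primary outcome from the sentence on the filter's scope, and confine the filter to the exploratory array genes. Add one sentence stating that IGF-1 and COX-2 are tested as prespecified, whatever their variability in the placebo arm. This restores the unfiltered power of 0.83 at 29 per arm.

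The cost is an amendment of wording, with no added patients, visits or assays. For the array genes, a filter that does not look at treatment arm, such as overall variance pooled over the three arms, would avoid selecting on the placebo result. That is optional and is not needed to resolve this point.
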